# Development of an App for Symptom Management in Women With Breast Cancer Receiving Maintenance Aromatase Inhibitors: Protocol for a Mixed Methods Feasibility Study

**DOI:** 10.2196/49549

**Published:** 2024-02-15

**Keywords:** acceptability, aromatase inhibitors, breast cancer, cancer, chemotherapy, disease, feasibility, inhibitor, management, mHealth, postmenopausal, psychosocial, QoL, quality of life, radiation therapy, symptom management, symptom, tool, treatment, usability, user-friendliness

## Abstract

**Background:**

Patients with postmenopausal nonmetastatic estrogen receptor–positive breast cancer often experience a reduced quality of life after primary treatment. The disease and treatment trajectory consists of surgery followed by chemotherapy or radiation therapy. Upon this, maintenance hormone therapy with an aromatase inhibitor can result in several physical and psychosocial symptoms. Optimal symptom control during maintenance therapy is central to maintaining the patient’s quality of life.

**Objective:**

This study aims to (1) develop an electronic symptom management tool for patients with postmenopausal early breast cancer receiving maintenance aromatase inhibitors with an endocrine aspect and (2) assess the feasibility, acceptability, and usability of the pilot version of the Bone@BC app. Furthermore, longitudinally, symptom prevalence and quality of life for patients with postmenopausal nonmetastatic estrogen receptor–positive breast cancer will be explored.

**Methods:**

This study follows a multistage research plan. In stage 1, a systematic literature review to establish an overview of aromatase inhibitor–related symptoms reported by postmenopausal women with nonmetastatic estrogen receptor–positive breast cancer will be completed. In stage 2, a comprehensive overview of symptoms related to aromatase inhibitors (letrozole, exemestane, and anastrozole) will be performed (eg, by reviewing medical leaflets and guidelines). In stage 3, an electronic app with a user-friendly Patient Concern Inventory list to comprise symptoms and concerns will be developed. Last, in stage 4, a convergent mixed methods feasibility study of the pilot version of the Bone@BC app will be conducted. A total of 45 patients with postmenopausal nonmetastatic estrogen receptor–positive breast cancer will use the app daily for symptom identification and respond to 6 serial patient-reported outcome measurements for 12 weeks. Finally, semistructured interviews will be performed. The primary outcome includes consent rate, attrition rate, retention rates, technical issues, and adherence, assessed using preestablished criteria on feasibility and a mixed methods approach for exploring acceptability. A patient advisory board consisting of 5 women with breast cancer is recruited to include their perspectives and experiences in the planning, organization, implementation, and dissemination of the research throughout the project.

**Results:**

At the time of submitting this paper (January 2024), a total of 23 patients have been included in the stage 2 medical audit over the recruitment period of 3 months (November 2022 to February 2023), and 19 patients have been enrolled in stage 2, the semistructured patient interviews.

**Conclusions:**

This protocol describes a study investigating the feasibility, acceptability, and usability of the symptom management tool Bone@BC developed for patients with breast cancer with an endocrine aspect.

**Trial Registration:**

ClinicalTrails.gov NCT05367830; https://clinicaltrials.gov/ct2/show/NCT05367830

**International Registered Report Identifier (IRRID):**

DERR1-10.2196/49549

## Introduction

### Breast Cancer

Patients with postmenopausal nonmetastatic estrogen receptor–positive (ER+) breast cancer (BC) in maintenance therapy with an aromatase inhibitor (AI) deal with numerous long-term cancer- and treatment-related side effects (eg, affected bone health). These side effects lead to impaired health-related quality of life (HRQoL) even years after ending primary treatment and during maintenance hormone therapy [1-3].

### The Transition

The transition from being closely monitored by specialists to fewer follow-up visits is difficult for the survivors of BC [4]. These difficulties are explained by reduced interaction with and less psychological support from health care professionals (HCPs) [5-8], as well as, in light of the less frequent consultations, the fact that their surroundings begin to consider the survivors of BC to be cured and healthy [9]. Still, patients during this trajectory stage must be capable of reacting sufficiently to the experienced side effects and potential symptoms [9]. Hence, understanding where and how information and support can be sought for these women is crucial [10] to optimize their self-efficacy and self-management [11].

### Patient-Reported Outcomes and Mobile Health

Patient-reported outcomes (PROs) are an important element in the person-centered care of patients with cancer [12,13]. Numerous applications have been developed to collect electronic patient-reported outcomes (ePROs) [14-16]. Mobile health (mHealth) apps have the potential to increase patients’ self-efficacy, strengthen empowerment, and offer value to patients in their daily lives [17,18]. The growing field of mHealth has been applied to numerous areas, including health promotion, behavior change support, and self-management of cancer diseases. mHealth is a subset of digital health, or eHealth, which also includes health information, telemedicine, and personalized medicine [19]. mHealth can be quickly scaled to reach thousands of people and potentially increase access to health care. mHealth is well-suited to symptom management, as it can provide timely dissemination of health information, encourage patients to acquire information during their communication with clinicians, and guide self-management.

### Hypothesis

We hypothesize that patients with postmenopausal nonmetastatic ER+ BC often experience reduced HRQoL after primary treatment due to treatment-related symptoms. Furthermore, transitioning from being closely monitored by HCPs to fewer follow-up visits can indeed be challenging for some patients. The close monitoring provided by HCPs can provide a sense of security and reassurance, and reducing the frequency of visits may therefore lead to feelings of uncertainty or anxiety. To help patients navigate this transition more smoothly, we will develop a symptom management tool in the form of a pilot version of the Bone@BC app. The pilot version of the Bone@BC app has the potential to significantly support patients in several ways, leading to an improved HRQoL and enhanced communication with HCPs. The app can include features that enable patients to monitor their symptoms regularly so that they will be able to act on them if necessary. It is important to note that the effectiveness of the Bone@BC app will depend on its design, functionality, and user experience. Conducting user testing and gathering feedback during the pilot phase will help identify areas for improvement and ensure that the app meets the specific needs of the target group of patients.

## Methods

### Study Design

This study follows a multistage feasibility design [20,21] comprising 4 stages (Figure 1 [21]).

As recommended in *Guidelines for Reporting Non-Randomized Pilot and Feasibility Studies* by Lancaster and Thabane [22], the reporting of the study protocol adheres to the CONSORT (Consolidated Standards of Reporting Trials) extension to pilot and feasibility trials.

**Figure 1 figure1:**
[figure not shown]
A multistage feasibility study. Convergent refers to the quantitative and qualitative data set being collected concurrently. Merge mean data will be analyzed separately and then merged according to allowing the research purpose from multiple perspectives. Metainferences refer to quantitative and qualitative results combined in a conclusion. ER: estrogen receptor; HRQoL: health-related quality of life.

### Study Setting

This study will be carried out as a single-center study at the endocrinology outpatient clinic at the Copenhagen University Hospital, Rigshospitalet, in Denmark.

### Recruitment

The patients will be recruited from the endocrinology outpatient clinic by clinicians at routine consultations. The semistructured interviews will be performed by the principal investigator ([name]) not being involved in the treatment and care of these patients. Patients will be screened for inclusion criteria during routine appointments. The informed consent can be withdrawn at any time. A screening log will be kept collecting reasons for nonresponses.

### Eligibility

The predetermined eligibility criteria are women aged between 50 and 70 years with a diagnosis of postmenopausal nonmetastatic ER+ BC; in maintenance therapy with an AI (letrozole, anastrozole, or exemestane); who are able to understand, read, and speak Danish; have access to a smartphone that can display the app (eg, iOS, iPADOS, or Android); and provide informed consent. Patients will be considered ineligible if they are unable to provide informed consent due to cognitive or linguistic inability, have a physiological or cognitive impairment that would prevent or inhibit the participation in using the app and answering the ePROs, have a previous malignancy, or are in maintenance therapy with tamoxifen.

### Patient and Public Involvement

Because patient involvement is essential for this study, to ensure patient-centeredness [23], a patient advisory board consisting of 5 women diagnosed with BC was recruited through an advertisement on the Danish Breast Cancer Organization’s website. The primary objective of the patient advisory board is to enhance the researcher’s communication and cooperation with patients, thereby ensuring the integration of their perspectives, requirements, experiences, and expectations throughout the various stages of research, including planning, organization, implementation, and dissemination [24,25].

### Intervention Description

#### The Proof-of-Concept Version of the Bone@BC App

Originally, a proof of concept of the Bone@BC app was developed (2015-2018) by a team of clinicians with specialist experience from the Healthy Living After Breast Cancer research group. The proof-of-concept app was published in 2 languages, Danish and English. The proof-of-concept version provides (1) advice on treatment elements (eg, blood samples and prevention); (2) daily questions about daily living; and (3) private notes. However, the proof-of-concept version of the app did not follow a systematic selection of symptoms to include, and no patients were involved in the design or content of the app (Figure 2).

**Figure 2 figure2:**
[figure not shown]
Overview of the proof-of-concept version of the Bone@BC app.

#### The Pilot Version of the Bone@BC App

The proof-of-concept version of the app yielded several noteworthy patient feedback examples, which are as follows:

Patients expressed the desire for an app that goes beyond educational purposes and provides support in their daily lives. Specifically, they highlighted the importance of having a tool that helps them remember changes in their symptoms.Patients emphasized the need for visual information, such as trends indicating their quality of life based on daily responses to HRQoL assessments.Patients expressed the expectation that the app should assist them in identifying relevant topics to discuss with HCPs.Some patients did not find the notes module in the app useful.Additionally, certain features such as blood samples, daily habits, and dual-energy x-ray absorptiometry scan were deemed unhelpful by patients.

This study seeks to develop a pilot version of the Bone@BC app based on the above feedback from the patients who used the proof-of-concept version of the Bone@BC app. The pilot version of the Bone@BC app will increase patient friendliness by implementing functionalities developed systematically in collaboration with patients and clinicians to solve patients’ specific needs using this symptom management tool (Table 1).

**Table 1 table1:** Overview of components in the proof-of-concept version versus the pilot version.

Components	Proof-of-concept version	Pilot version
Information on treatment-related osteoporosis, blood samples, and physical activity (both text and video) with health care professionals	✓	✓
Training instructions videos		✓
My progress	✓	
My results (eg, blood samples)	✓	
My medication (eg, breast cancer medication)	✓	
Body measures (height and weight)	✓	
Daily habits	✓	
Activity from your mobile phone health tracker		✓
My notes	✓	
Feedback	✓	✓
Patient Concerns Inventory prompt list		✓
Reminder module		✓
Reminder list based on the previous Patient Concerns Inventory prompt list		✓
Intelligent progress of the health-related quality of life measurements		✓
Trends for the health-related quality of life measurements (tendencies algorithm)		✓
Simplified user interface		✓
Danish version	✓	✓
English version	✓	✓

### Definition of Symptoms

Our study will use the definition of symptoms from the National Institutes of Health and the National Cancer Institute: “A physical or mental problem that a person experiences that may indicate a disease or condition. Symptoms cannot be seen and do not show up on medical tests. Some examples of symptoms are headache, fatigue, nausea, and pain” [26].

### Development of the Pilot Version of the Bone@BC App

To develop the pilot app version, this multistage study consists of 4 stages (Figure 1) where the Bone@BC app will be further developed and then tested in a feasibility study.

#### Stage 1

A systematic review will be undertaken to appraise the current literature and provide an overview of AI-related symptoms reported by postmenopausal women with nonmetastatic ER+ BC. The systematic literature review will be reported according to the PRISMA-P (Preferred Reporting Items for Systematic Review and Meta-Analysis for Protocols) 2015 statement [27]. A comprehensive search will be undertaken on the following databases: PubMed, MEDLINE, CINAHL, Embase, Cochrane, Web of Science, PsycINFO, and Scopus. The Mixed Methods Appraisal Tool version 2018 [28] will be used for assessing the included studies’ methodological quality.

#### Stage 2

Stage 2 will be an explorative multimethod stage relying on patient involvement. Moreover, symptoms and concerns identified by the European Organization for Research and Treatment of Cancer (EORTC) Library Item [29] will be selected to be included in the Bone@BC app.

Multimethod data collection will be carried out to explore the symptoms reported by the patients with postmenopausal nonmetastatic ER+ BC in maintenance therapy with AI (letrozole, anastrozole, and exemestane; Figure 3).

**Figure 3 figure3:**
[figure not shown]
Study assessments in stage 2. EORTC: European Organization for Research and Treatment of Cancer.

A summary of pharmacological products at the European Medicines Agency [30] and the Food and Drug Administration [31].Review of medical leaflets at the website Medicine.dk [32].Reviews of international and national guidelines for the standard clinical practice: oncological (American Society of Clinical Oncology [33], European Society for Medical Oncology [34], and Danish Breast Cancer Group [35]) and endocrinological (Endocrine Society [36], European Society of Endocrinology [37], and Danish Endocrinological Society [38]).Medical record audit from patients with postmenopausal nonmetastatic ER+ BC. The inclusion period will be from November 14, 2022, to February 14, 2023. All patients attending routine consultations will be invited to participate. The principal investigator will perform the reviews and exclude patients who do not meet the predetermined inclusion criteria.Semistructured face-to-face patient interviews on symptom experience (n=15-20).The quantitative and qualitative results from steps 1 to 5 will, together with the systematic literature review, provide a comprehensive overview of the symptoms, side effects, and concerns that patients with postmenopausal early BC are dealing with. These symptoms and concerns will be organized into domains for HRQoL measurements to identify related and validated items in the EORTC Library that can be implemented in the pilot version of the Bone@BC app daily questions [29].Finally, a harmonization meeting will be organized, initially involving the patient advisory board, followed by the interdisciplinary research group (the authors). The purpose of this meeting will be to facilitate discussion, collaboration, and consensus among participants regarding the selection of specific items from the EORTC Library [39].

#### Stage 3: Multimethod Exploratory Study

In this stage, an electronic Patient Concerns Inventory list (PCI) will be adapted from the English version of the PCI developed by Kanatas et al [40] for patients with BC. The adapted PCI will be modified to fit the app. A PCI is a structured list of frequently asked questions and concerns. It is designed to support and encourage patients to acquire information during their communication with HCPs. The development of the electronic PCI relies on the following steps: (1) translation and linguistic validation according to the Professional Society for Health Economics and Outcomes Research [41]; (2) focus group interview with the patient advisory board; (3) development of a minimum variable product (MVP) app only to test the electronic PCI list; (4) the patient advisory board testing the MVP app and evaluating it in a focus group interview; (5) pilot-test patients (n=15) using the MVP app will be interviewed by semistructured face-to-face interviews; and (6) harmonization meeting in the multidisciplinary research team.

The identified items from the EORTC Library [39] and the PCI will be implemented in the pilot version of the Bone@BC app.

#### Stage 4

Stage 4 is a convergent, nonrandomized, single-arm mixed methods feasibility study [21] (Figure 4 [20,21,42-49]) investigating the feasibility of the pilot version of the Bone@BC app.

The purpose of this stage will be to explore the patients’ perspectives on feasibility, acceptability, and usability while being offered the pilot version of the Bone@BC app, which will be provided to them as a tool for symptom identification over a period of 12 weeks. Moreover, the consent rate, attrition rate, adherence rate, and retention rate will be explored. Furthermore, the potential changes in self-efficacy, HRQoL, and patient empowerment over time will be measured. The findings from the quantitative data (PRO questionnaires and data in the Bone@BC app) and the qualitative data (patient interviews) will be compared and merged. The intent is to obtain a more comprehensive understanding of the feasibility, usability, barriers, and subgroup of patients who may benefit from using the app.

**Figure 4 figure4:**
[figure not shown]
Stage 4: convergent mixed methods feasibility study. Convergent mean that the quantitative and qualitative data sets are collected concurrently, analyzed separately, and then merged accordingly to achieve the research purpose from multiple perspectives. After analysis of each data set, inferences will be drawn. At the end of the study, the metainferences will be drawn and included in the larger interpretation being made in the study’s discussion section. Consecutive sampling refers to every participant who meets the criteria of inclusion and is selected until the required sample size is attained [50]. Purposeful sampling refers to the researcher intentionally recruiting participants who have experienced the central phenomenon being explored in the study. Matomo refers to an open-source digital analytics platform (Matomo). EORTC QLQ-C30: European Organization for Research and Treatment of Cancer Quality of Life C30; HADSA: Hospital Anxiety and Depression Scale; heiQ: Health Education Impact Questionnaire; HRQoL: health-related quality of life; PROM: patient-reported outcome measure; SES6G: Self-Efficacy for Managing Chronic Disease 6-Item Scale; SGPALS: Saltin-Grimby Physical Activity Level Scale; SUS-DK: System Usability Scale–Danish version.

### Measures

#### Feasibility

The feasibility of the study will be assessed by the rate of recruitment and retention over the study duration (12 weeks). The feasibility parameters include adherence rate, acceptability, response rate, representativeness, recruitment rate, technical difficulties, and satisfaction [51].

#### Acceptability

The acceptability of the pilot version of the Bone@BC app will also be explored by semistructured interviews with a subgroup of the 40-50 invited participants in the study.

#### Usability

The satisfaction survey will be the System Usability Scale–Danish version (SUS-DK) [42] and will be explored in semistructured patient interviews after the intervention. The System Usability Scale is a 10-item questionnaire with 5 responses ranging from “strongly disagree” to “strongly agree” [42]. The final question allows respondents to provide further comments in an open-ended format. The criteria for being satisfied will be a system usability score of ≥68% [42].

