**PRO^j^ data through the app**																										
	Electronic patient-reported PRO questionnaires on symptoms Bone@BC (everyday)^k^	✓		✓		✓		✓	✓		✓		✓		✓		✓		✓		✓		✓		✓	
Semistructured interviews																										✓

^a^REDCap: Research Electronic Data Capture.

^b^Demographic data (eg, marital status, family status, educational level, and occupation).

^c^EORTC QLQ-C30: European Organization for Research and Treatment of Cancer Quality of Life C30.

^d^SES6G: Self-Efficacy for Managing Chronic Disease 6-Item Scale.

^e^heiQ: Health Education Impact Questionnaire.

^f^HADS: Hospital Anxiety and Depression Scale.

^g^SGPALS: Saltin-Grimby Physical Activity Level Scale.

^h^SUS-DK: System Usability Scale–Danish version.

^i^Open-source web analytic platform Matomo Analytics.

^j^PRO: patient-reported outcome.

^k^Patient-reported outcomes from the app on the questions provided daily on health-related quality of life, late side-effects, symptoms and concerns perspectives, and level of physical activity in the Bone@BC app and question prompt list. Items developed in stage 3 and implemented from the European Organization for Research and Treatment of Quality of Life Item Library in the domains of late side-effects and symptoms management.

The health-related ePROs being assessed before and after the study will be the HRQoL by the 30-item EORTC Quality of Life C30 (QLQ-C30) [44]. The HRQoL domains are divided into multi-item subscales: functional (physical, role, cognitive, emotional, and social), symptom (fatigue, pain, nausea/vomiting, and dyspnea), financial adversity, and global health status [44]. The EORTC-QLQ-C30 has proven to be reliable and valid in a range of patient populations and a variety of treatment settings [52].

Self-efficacy will be measured by the Self-Efficacy for Managing Chronic Disease 6-Item Scale (SES6G) [45]. SES6G is a self-administered questionnaire with 6 items on the patient’s perceived self-efficacy on a 10-point Likert scale ranging from “not at all confident” to “totally confident” [45]. Ritter and Lorig [53] conducted 2 new studies and reviewed 8 independent studies to investigate the psychometric properties of the scale. Cronbach α was a minimum of .88 across all studies; minimal floor and ceiling effects were observed; the measure was sensitive to change; and moderate and significant correlations provide convergent validity evidence when measured against selected health indicators [53].

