### Statistical Analysis

#### Preestablished Criteria

Feasibility will be explored by looking at the success threshold, attrition rate, and adherence. The success threshold of ≥60% will be defined as the proportion of informed patients giving consent. The attrition rate will be calculated as the proportion of participants withdrawing from the intervention, leaving no data on outcomes available. The retention rate of ≥85% will be the number of individuals who remained in the study and responded to the daily PRO in 12 weeks. The retention rate and success threshold are based on a recent systematic review of internet-based supportive care for patients with lung disease [57]. Patient adherence will be the proportion of patients completing self-reports for each time point adjusted for withdrawals. The adherence rate is the proportion of patients replying to ≥80% of the daily PRO questions. Adherence to daily completion will be analyzed according to, for example, material status and educational level using the Fisher exact test.

Acceptability will be assessed based on the following predetermined criteria: (1) system usability score ≥68% [42]; (2) patients’ experience identified in follow-up interviews; and (3) HRQoL must be at least at the same level before and after the intervention as measured by the EORTC QLQ-C30 [44].

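### Usability scores and acceptability interviews are due only at week 12, so women who withdraw are not heard and acceptability risks upward bias; earlier-stage participants are also not kept out of Stage 4

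*Protocol article*

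**What the plan says.** Under Measures, Usability, the satisfaction survey is SUS-DK, and usability "will be explored in semistructured patient interviews after the intervention". In Table 2, SUS-DK has a single tick, in the same final position as the week-12 tick of the other questionnaires. The row "Semistructured interviews" also has one tick, in the last column.

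Under Preestablished Criteria, "Acceptability will be assessed based on the following predetermined criteria: (1) system usability score ≥68" opens a list of three. The second criterion is patients' experience from follow-up interviews. The third is QLQ-C30 no worse after the intervention than before. The same section defines attrition as withdrawal from the intervention with no outcome data left, and sets retention at 85% or more.

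The Acceptability section describes "semistructured interviews with a subgroup of the 40-50 invited participants in the study". The Figure 4 caption defines purposeful sampling as "the researcher intentionally recruiting participants who have experienced the central phenomenon being explored in the study". Neither reserves places for women who stopped.

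On who may enter Stage 4, the Eligibility section closes its exclusions with "have a previous malignancy, or are in maintenance therapy with tamoxifen" and does not mention earlier participation. Recruitment is from one endocrinology outpatient clinic, and the Figure 4 caption describes consecutive sampling of everyone who meets the criteria. In Stage 3, "pilot-test patients (n=15) using the MVP app will be interviewed by semistructured face-to-face interviews". Stage 2 plans 15 to 20 patient interviews, and the Results report 19 women enrolled.

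**The concern.** A woman who withdraws because the app is hard to use is the most informative witness on usability, and the schedule has no point at which she is asked. The two acceptability criteria that rest on SUS-DK and the interviews would then describe only those who stayed. This cuts against the Stage 4 aim of understanding barriers and which patients may benefit, and against representativeness, which the Feasibility section lists as a parameter.

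The second issue concerns entry. The Stage 3 testers use an early app that carries the electronic Patient Concerns Inventory, and that list is then built into the pilot app. If some of them enter Stage 4, they rate a component they have already used and commented on. They may also be readier to consent and to stay. The pass marks for SUS, consent (60%) and retention (85%) would then be judged partly on women unlike the future user.

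**Working it through.** The article gives no expected SUS, standard deviation or dropout figure, so there is no figure of its own to reproduce. What follows is sensitivity arithmetic. It assumes that the 68 criterion is applied to the group mean.

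**1. How many women may lack a SUS.** The sample size is 40-50 (Power section), with 45 in the abstract. The smallest whole number that meets 85% retention is 34 of 40, 39 of 45 or 43 of 50, which leaves 6, 6 or 7 women. Treating these as the women without a SUS is an assumption.

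**2. Effect on the SUS verdict at N = 45.** Let m be the mean in the 39 women measured and u the mean the other 6 would have given.

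- Mean over all 45 = (39m + 6u)/45.
- Break-even u = (68 × 45 − 39m)/6 = (3060 − 39m)/6.

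| Observed m | Break-even u |
|---|---|
| 70 | (3060 − 2730)/6 = 55.0 |
| 72 | (3060 − 2808)/6 = 42.0 |
| 75 | (3060 − 2925)/6 = 22.5 |

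With m = 70 and u = 50, the mean over all 45 is (2730 + 300)/45 = 67.3, below 68, although the reported SUS and the retention rate (39/45 = 86.7%) both pass. With u = m the bias is zero.

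If only 70% were measured, an observed 70 would reverse below (68 − 0.70 × 70)/0.30 = 63.3. Retention would then probably have failed as well, so the loss would be visible.

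**3. Effect of earlier-stage participants on SUS.** If k of 45 women come from earlier stages and score d points higher, the mean rises by (k/45) × d.

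| k | d = 2 | d = 5 | d = 10 |
|---|---|---|---|
| 0 | 0 | 0 | 0 |
| 5 | 0.2 | 0.6 | 1.1 |
| 15 | 0.7 | 1.7 | 3.3 |
| 34 | 1.5 | 3.8 | 7.6 |

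The last row is a ceiling: all 19 interviewees and all 15 testers, with no woman in both groups, enter Stage 4. Every k and d is assumed.

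**4. Effect on retention.** If all 15 testers enter and all stay, and 24 of 30 new users stay, the pooled rate is 39/45 = 86.7% (pass), while new users are at 24/30 = 80% (fail). If one tester leaves, the pool is 38/45 = 84.4% and fails, so the illustration needs every tester to stay.

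**The case against.** A usability score has to follow use, so a week-12 SUS-DK is not an error in itself. This stands: the gap is the absence of a score at exit.

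Stopping app use is not the same as withdrawing. Table 2 lists SUS-DK with the REDCap data, apart from the in-app questions, so a woman who abandons the app but stays in the study is still due a SUS-DK. Interviewees are drawn from all invited participants, and the sampling definition does not bar women who withdrew. This also stands, and it limits the point to women who withdraw. The set lacking a SUS need not match the set not retained, because retention also requires response to the daily questions.

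Loss is not hidden either. Attrition, retention, adherence and technical issues are assessed, Matomo tracks use, and a screening log records reasons for nonresponse. But none of these is stated to record how usable a woman who left found the app.

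A reader might go further and infer that acceptability is measured in favourable users and is biased upward. The article does not show this. Women may withdraw for unrelated reasons. The article does not say that any earlier-stage woman will enter Stage 4 or that she would score higher, and the full protocol may deal with overlap. Consecutive sampling is no safeguard, however, since as described it admits any eligible woman.

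A reader might also take "All patients attending routine consultations will be invited to participate" to mean that the whole clinic has been exposed. That sentence concerns the medical record audit, which involves no use of the app. The Stage 2 interviews are about symptoms, and the Stage 3 app tests only the concerns list, so exposure is partial. The advisory board was recruited through a patient organization's website, which makes its overlap less likely.

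Finally, the SUS timing cannot raise consent or retention. Only prior exposure could do that.

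**Conclusion.** The point holds as a risk of upward bias. Followed as written, the schedule leaves two of the three acceptability criteria without the views of women who withdraw. The third criterion has a baseline measurement and does not rest on week 12 alone.

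The size depends on how close the result is to the threshold. At 39 of 45 measured, an observed mean of 70 reverses if the missing 6 would average below 55, whereas an observed 75 is robust to all but very low scores. The direction rests on the assumption that women who withdraw would rate the app lower.

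Prior exposure is a separate and less certain issue. The eligibility list and consecutive sampling at one clinic permit it, but its extent is unknown. It ranges from no effect with no overlap to about 1.7 SUS points if 15 of 45 women had earlier contact and scored 5 points higher.

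**What to change.** Offer SUS-DK and a brief exit interview at withdrawal. Include in the purposeful interview sample women who withdrew or who answered under 80% of the daily questions. Report the 68 criterion on the last available SUS of every woman who opened the app, alongside the result in week-12 completers.

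Record any earlier participation (Stage 2 interview, Stage 3 testing, advisory board) at Stage 4 entry, and report consent, retention, adherence and SUS separately in new users. Consent in new users requires the flag to be kept in the screening log too. Flagging is preferable to exclusion: shutting out up to 34 women (19 + 15) could slow recruitment in a clinic whose audit included 23 patients in three months.

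The cost is a 10-item questionnaire and a short conversation per withdrawal, plus one data field. Some women who withdraw will decline, and exit scores will reflect shorter use, which is why both SUS results should be shown. The Results section reports enrolment only for Stage 2, so the change appears possible before Stage 4 begins. Exit ratings not collected then cannot be recovered later.
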